## Abstract

**Background:**

Black women and people with uteri have utilized collectivistic and relational practices to improve health outcomes in the face of medical racism and discrimination for decades. However, there remains a need for interventions to improve outcomes of uterine fibroids, a condition that disproportionately impacts Black people with uteri. Leveraging personalized approaches alongside evidence that demonstrates the positive impact of social and peer support on health outcomes, we adapted from *CenteringPregnancy*, an evidence based group prenatal care intervention, for the education and empowerment of patients with uterine fibroids.

**Methods:**

The present report provides  an overview of the study design and planned implementation of CPWF in cohorts at Boston Medical Center and Emory University / Grady Memorial Hospital. After receiving training from the Centering Healthcare Institute (CHI), we adapted the 10-session *CenteringPregnancy* curriculum to an 8-session hybrid group intervention called *Centering Patients with Fibroids* (CPWF). The study began in 2022 with planned recruitment of six cohorts of 10-12 participants at each institution. We will conduct a mixed methods evaluation of the program using validated survey tools and qualitative methods, including focus groups and 1:1 interviews.

**Discussion:**

To date, we have successfully recruited 4 cohorts at Boston Medical Center and are actively implementing BMC Cohort 5 and the first cohort at Emory University / Grady Memorial Hospital. Evaluation of the program is forthcoming.

## Background

Despite major advances over the past several decades, the medical field has made minimal progress in addressing health disparities, especially in maternal and reproductive health. The Black Women’s Health Imperative, an organization founded to address health disparities and reproductive rights of Black women, recently celebrated their 40 year anniversary [1]. The organization’s premier event was the first National Conference on Black Women’s Health Issues held at Spelman College in Atlanta, Georgia in 1983. In a letter addressed to conference attendees, founder and reproductive health leader Byllye Y. Avery raised a call to action: “The conception of this project and the birth of this Conference are no coincidence.…Our presence at this "conference of the decade" indicates our commitment to improving the health of Black women and our support of the Women’s Health Movement…The time to rise to action is NOW!” [2]. Avery’s conference of nearly 2,000 attendees, the coming together of “self-help group” members from around the country, reframed racism in women’s health in the public, medical, and academic spheres, and provided group space for Black women to share experiences and collaborate towards systemic solutions. The 3-day conference was a pivotal event in the history of reproductive health and rights advocacy, and 40 years later, Black women continue to experience disproportionately negative health outcomes on nearly every indicator of reproductive health. Thus, community organizing and novel interventions for Black reproductive health remain relevant and needed today.

Uterine fibroids (UF), non-cancerous smooth muscle tumors of the uterus, are the most common tumor in people with uteri and disproportionately impact Black people and those of African ancestry [3–10]. Black people with UF report feeling dismissed [11], undervalued [11], and encouraged to seek hysterectomy when they would prefer uterine and/or fertility-sparing management options [12]. Implicit racial bias within the healthcare system has been directly linked to delivery of lower quality care for Black patients [13]. Such practices, identified as medical racism, affect Black patients’ decisions to seek care for symptomatic UF, provider perceptions of patient pain and symptoms, and treatment options offered for UF management.

In the field of Obstetrics and Gynecology, *CenteringPregnancy* is lauded as a standout intervention to improve maternal and neonatal outcomes. *CenteringPregnanc*y combines group education with individual directed prenatal care for pregnant patients with a similar estimated due date. *CenteringPregnancy* group sessions include pregnant patients and providers discussing nutrition, stress management, labor and delivery, breastfeeding, and infant care in addition to routine aspects of the clinical visit. Participation in *CenteringPregnancy* has led to decreased rates of preterm and low birth weight infants, an increase in breastfeeding/chestfeeding rates, and increased spacing between pregnancies [14].

Another key aspect of the intervention is our partnerships with community and national advocacy groups, The White Dress Project (TWDP) and the Boston-based Resilient Sisterhood Project (RSP). The White Dress Project (TWDP) is a national nonprofit patient advocacy organization dedicated to raising global UF awareness through education, research, and community-building. Since its founding in 2014, TWDP has established the month of July as Fibroid Awareness Month in the US House of Representatives, lobbied successfully for the Stephanie Tubbs Jones Fibroid Research and Education Act, and curated educational webinars, regional events, and a robust social media presence. RSP is a Boston-based nonprofit that supports the gynecological health of women of African descent whose members and executive director assisted in the first cohort of CPWF.

Group-based models of care contribute to the development of a network of patients, providers, and peer advocates who work together to prioritize patients and improve health outcomes, creating spaces ripe for promoting health education and literacy while inspiring patient autonomy. Our team adapted the *CenteringPregnancy* model to develop and implement a group education model, *Centering Patients with Fibroids* (CPWF), an intervention that we hypothesize will improve knowledge, self-advocacy, reproductive health outcomes, and quality of life for black patients with UF.

## Methods/design

This pilot prospective cohort trial will utilize a concurrent mixed-methods design to obtain information about intervention feasibility, acceptability, and sustainability and assess preliminary evidence of improved outcomes.

### Intervention

We will implement *Centering Patients with Fibroids* (CPWF) at Boston Medical Center (BMC) and Grady Memorial Hospital/Emory University Hospital Midtown, two academic-based safety net hospitals that serve racially and socioeconomically diverse patient populations in different regions of the United States. The investigation of patients at these two hospitals will help to detect any existing regional differences in implemention. The study was approved by the Institutional Review Board at both institutions. Eligible participants include patients between the ages of 18 to 45 years old receiving care at one of the study hospitals, with symptomatic UF measuring equal or more than 2 cm, and uterine dimensions of less than 20 cm on pelvic imaging within 12 months of recruitment. Exclusion criteria include inability to speak English, pregnancy at time of recruitment, and no available pelvic imaging. Eligible and interested patients will provide informed consent to participate in an 8-week education and empowerment program, conducted in person and via Zoom in a hybrid modality. Each 1.5 h session will be facilitated by the study site principal investigator (PI), research staff trained in group facilitation by the Centering Healthcare Institute (CHI), and/or members of our advocacy partner, The White Dress Project.

Our investigative team adapted the components of the *CenteringPregnancy* program, a group model of prenatal care developed through the Centering Healthcare Institute (CHI), to design a complementary education and empowerment program for patients with UF. CHI’s group care framework prioritizes high quality healthcare, interactive learning, and positive health outcomes through building relationships and community among group members. To apply and adapt this model to serve the needs of patients with UF, our research team members were first trained as certified Centering facilitators. CHI facilitator training provides a broad range of strategies for both virtual and in-person engagement, including mindfulness activities, storytelling exchanges, writing exercises, and “ball-toss” interactive conversations. Storytelling exchanges in particular can help to empower and improve patient engagement in their own care by sharing personal experiences [15, 16]. In the broader context, storytelling also has the power to reduce health disparities [17]. Our team used the skills gained from this facilitation training to create CPWF as a group-based care model focused on providing exceptional care to patients with UF through a multidisciplinary, patient-centered, conversational, and evidence-based approach. CPWF curriculum topics mirror *CenteringPregnancy* and include the role of environment and diet on UF; impact of UF on mental health, fertility and pregnancy, bleeding and anemia, and pain; and UF treatments including non-surgical medical therapies, uterine-sparing procedures, and hysterectomy (Fig. 1). Program participants receive detailed information on all of the surgical and non-surgical options for managing UF and have the chance to discuss their options with peers and clinical staff.

**Fig. 1 Fig1:**
[figure not shown]
Adapting the CenteringPregnancy model for uterine fibroids

Healthcare advocates from TWDP co-facilitate each session to aid in maintaining a patient-centered experience.

CPWF cohorts are implemented using a hybrid modality, with the first and last sessions conducted in person, and the remaining sessions conducted via Zoom (Fig. 1). A total of 7 cohorts will receive the program at BMC, and a total of 6 cohorts will receive the program at Emory/Grady. All CPWF participants complete a “Dear Fibroids” letter to their fibroids at the beginning of the session, a personal effort to define and process how fibroids have impacted their daily lives. We utilize Zoom features such as breakout rooms, screen sharing, and polls for greater engagement in the virtual space. For example, one strategy for online engagement includes activities to establish rapport between patients via Zoom breakout rooms, focused on discussing fibroid experiences, unique or fun facts about participants, and hobbies. Other strategies include mindfulness activities, “ball toss” activities to reinforce learning in a playful way, and artistic exercises such as drawing in the “Past, Present and Future” exercise in which participants color a tree with branches symbolizing various stages in their fibroid journey.

### Recruitment

Participants will be recruited from the Fibroid Center and Obstetrics and Gynecology (OBGYN) clinics at Boston Medical Center, Emory University Hospital Midtown, and Grady Memorial Hospital. Participants will be identified using the BMC, Emory University Hospital Midtown and Grady Memorial Hospital Electronic Medical Records (EMR), Epic MyChart, clinic schedule, and flyers placed in high-traffic areas in the clinical space (Fig. 2). Potential participants may also be referred from OBGYN providers in the clinic if they meet criteria. A research team member reaches out to patients who meet inclusion criteria by phone or during an in-person clinic encounter to inquire about interest in participating in the study. If a candidate for the study agrees to participate, a trained study researcher/interviewer will contact the subject and explain what the study entails to obtain informed consent.

**Fig. 2 Fig2:**
[figure not shown]
Centering Patients with Fibroids (CPWF) recruitment and participation flow

In addition to these screening and recruitment practices, we used EPIC/MyChart to reach patients not seen in the OB/GYN practice who are diagnosed with UF. We obtained a list of non-pregnant patients with fibroid diagnoses as a preliminary eligibility screening, then sent a study recruitment letter with Opt Out language to the patient’s MyChart inbox. We posted digital flyers with QR codes on waiting room television monitors in clinics throughout the hospital to supplement paper recruitment flyers. We reached out to the Family Medicine and General Internal Medicine departments at BMC and Emory/Grady to identify provider research champions to assist us in identifying potentially eligible patients/connecting them with the study opportunity through MyChart. Finally, we will access emergency department and gynecology follow up referral lists to screen patients for CPWF and reach out to potentially eligible subjects. Participants will be remunerated up to $200 via reloadable gift cards called “ClinCards” for survey completion, lab draw, and session attendance. We emphasize that CPWF is a program designed to complement, rather than replace, one-to-one gynecological care with a participant’s provider.

In addition to recruiting patients, we recruited healthcare leaders and providers at Boston Medical Center, Emory University Hospital Midtown, and Grady Memorial Hospital to participate in interviews. We will identify those who are invested in improving access to quality care and health outcomes for patients seeking care at BMC, Emory University Hospital Midtown, and Grady Memorial Hospital. Interviewees will be leaders and providers who have had some level of contact with the Fibroid Center, Emory University Hospital Midtown, and Grady Memorial Hospital or provide care to women seeking care related to symptomatic uterine fibroids. They are contacted via email and asked to participate. If they agree, we will obtain consent and schedule interviews.

### Quantitative methods

To assess preliminary program impact on physical and mental health outcomes, participants will complete self-reported surveys during their participation in this study: pretest, posttest, and 3 month follow up. The surveys will include demographic questions and a series of validated measures, including the Uterine Fibroid Symptom and Quality of Life (UFS-QOL), the Everyday Discrimination Scale, Patient Health Questionnaire-9 (PHQ-9), and the Instrument for Evaluation of the Experience of Chronic Patients (IEXPAC).

As the aim of this pilot study is to assess preliminary outcomes as well as feasibility, acceptability, and sustainability, achieving a predetermined sample size for power was not necessary. We anticipate 10-12 participants per cohort for a total of 13 cohorts, 7 at BMC and 6 at Emory/Grady. As such, we will perform comparison of mean scores of the various validated survey instruments using analysis of variance (ANOVA) tests. We will also ask participants to give blood for serum studies including complete blood count (CBC), Anti-Müllerian hormone (AMH), and 25-OH-Vitamin D. Values will be compared at baseline and 3 months after the program completion. We hypothesize decreased anemia and vitamin D deficiency among program participants at 3 month follow up, and variable change in the AMH level related to the age at the time of program participation.

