Our study group will describe the experiences of participants and feedback from providers and other healthcare leadership on program implementation and will identify modifiable intervention targets and organizational, provider, and patient level factors associated with successful implementation of CPWF. Quantitative data include survey results and serial lab values for hemoglobin, hematocrit, vitamin D, iron studies, and AMH. Hemoglobin and hematocrit are markers of anemia, which is prevalent in patients with heavy menstrual bleeding due to UF [30]. Vitamin D deficiency is a possible risk factor for UF occurrence. Vitamin D concentrations have been found to be inversely associated with uterine fibroid prevalence, especially in Black women [31]. AMH is used as a marker of functional ovarian reserve [32] and is thus valuable in counseling women about reproductive and treatment planning in the setting of gynecological conditions such as UF [33]. The combination of both qualitative and quantitative methods will allow us to capture the benefits of CPWF over a shorter timeframe and to lay the groundwork for larger studies. We will use the data from our mixed methods study to direct next steps, including future iterations of the curriculum in response to feedback from participants, faculty, clinicians, and other key stakeholders, and a larger multisite randomized controlled trial to further explore the efficacy and generalizability of CPWF across the country.

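### The overall ANOVA stated for the four surveys has no direction and cannot separate lasting from vanished change; within-participant changes with confidence intervals would answer the question asked

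*Protocol article*

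**What the plan says.** The relevant text is in the protocol article, Methods/design, Quantitative methods. The purpose of the surveys is given as "To assess preliminary program impact on physical and mental health outcomes". On timing, "participants will complete self-reported surveys during their participation in this study: pretest, posttest, and 3 month follow up". The instruments are "a series of validated measures, including the Uterine Fibroid Symptom and Quality of Life (UFS-QOL), the Everyday Discrimination Scale, Patient Health Questionnaire-9 (PHQ-9") and IEXPAC. For the analysis, "we will perform comparison of mean scores of the various validated survey instruments using analysis of variance (ANOVA) tests". The sentence does not name the ANOVA factor, a time contrast, a direction, or an instrument that comes first.

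The expected direction appears in the Background, which describes the programme as "an intervention that we hypothesize will improve knowledge, self-advocacy, reproductive health outcomes, and quality of life for black patients with UF". The Discussion says that the qualitative and quantitative methods together "will allow us to capture the benefits of CPWF over a shorter timeframe and to lay the groundwork for larger studies", and mentions a larger multisite randomized trial as a next step.

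The laboratory values are handled separately. They are "serum studies including complete blood count (CBC), Anti-Müllerian hormone (AMH), and 25-OH-Vitamin D", compared between baseline and 3 months after the programme. A direction is stated for two of them: "We hypothesize decreased anemia and vitamin D deficiency among program participants at 3 month follow up". AMH is expected to vary with age.

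**The concern.** The hypothesis is one of improvement. The stated test is, on its most favourable reading, a repeated-measures ANOVA over three visits, whose overall F test has the null hypothesis that all three means are equal. Rejecting it says that something changed. It does not say whether scores rose or fell, or whether a change at the end of the programme was still there 3 months later.

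For a short programme (8 weeks), persistence is a main thing a reader will want to know. It is also what a planner of the later randomized trial would need, together with an estimate of the size and variability of the change. An F-test p-value supplies none of these. With four instruments on an equal footing, one isolated small p-value could also be read as programme impact.

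**Working it through.** **Figures to reproduce.** None. The article states no alpha, effect size, standard deviation or power. The only arithmetic is the planned size: 7 + 6 = 13 cohorts of 10-12, so 13 × 10 = 130 to 13 × 12 = 156 participants.

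**Inputs.**
- From the article: four named instruments, three survey time points, 130-156 participants.
- Assumed: two-sided 0.05 per test, a shift of 0.3 SD, within-person correlation ρ = 0.5 (equal between all visits), no dropout, and between-instrument correlation from 0 to 0.8.

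**Step 1: what the F test responds to.** With equal correlation between visits, the power of the repeated-measures F test depends on the means only through λ = N × Σ(μ_t − μ̄)² / (1 − ρ), with means in SD units. For four patterns (pretest, posttest, 3 months):

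| Pattern | Means | μ̄ | Σ(μ_t − μ̄)² |
|---|---|---|---|
| Gain that vanishes | 0, 0.3, 0 | 0.1 | 0.01 + 0.04 + 0.01 = 0.06 |
| Lasting gain | 0, 0.3, 0.3 | 0.2 | 0.04 + 0.01 + 0.01 = 0.06 |
| Delayed gain | 0, 0, 0.3 | 0.1 | 0.01 + 0.01 + 0.04 = 0.06 |
| Worsening | 0, −0.3, −0.3 | −0.2 | 0.04 + 0.01 + 0.01 = 0.06 |

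All four have λ = 130 × 0.06 / 0.5 = 15.6 at N = 130. The noncentral F distribution with 2 and 258 degrees of freedom then gives power 0.950 for every pattern. At N = 156, λ = 18.72 and power is 0.978. Under these assumptions the test treats the four patterns identically, whatever N or shift is chosen.

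**Step 2: confirmation by simulation** (4,000 trials per pattern).

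| Pattern | F test, N = 130 | 3 months vs pretest, N = 130 | F test, N = 156 | 3 months vs pretest, N = 156 |
|---|---|---|---|---|
| Gain that vanishes | 94.6% | 4.8% | 98.0% | 5.0% |
| Lasting gain | 94.8% | 92.2% | 97.6% | 95.8% |
| Delayed gain | 95.0% | 92.9% | 97.8% | 96.2% |
| Worsening | 95.2% | 92.3%, none favourable | 97.9% | 95.7%, none favourable |

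Hand check of the contrast: the SD of a within-person change is √(2 × (1 − 0.5)) = 1, so 0.3 × √130 = 3.42. The paired t test then has power 0.924, in line with the 92.2% simulated.

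With 100 completers instead, a separate simulation (1,500 trials per pattern) gave an F test significant in 86% for the vanishing gain and 89% for the delayed gain. The 3-month contrast was significant in 4% and 85%.

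**Step 3: four tests on an equal footing.** Under no change and with independent instruments, the chance of at least one p<0.05 is 1 − 0.95⁴ = 0.185. Simulating equally correlated two-sided tests (300,000 draws) gives 18.6%, 17.3%, 15.6% and 11.3% at between-instrument correlation 0, 0.3, 0.5 and 0.8. That is about 11-19%, against 5% for one named contrast.

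**Step 4: what the replacement delivers.** With the same assumed correlation, the 95% CI for a mean change has half-width 1.96 / √130 = 0.17 SD (1.96 / √156 = 0.16 SD). That estimate, with its SD of change, can be used in planning a randomized trial.

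**The case against.** The strongest case against is that this is a condensed article about a pilot. Its stated aims include feasibility, acceptability and sustainability, it calls the outcome evidence preliminary, and it sets no alpha and no success rule. Follow-up contrasts, a main outcome or a multiplicity rule may sit in an analysis plan that is not shown. The means at each visit would also show a careful reader the direction and persistence. All of this stands, and it keeps the severity low. It does not rescue the stated method: the sentence commits the survey analysis to ANOVA tests, and the overall F test does not bear on improvement. Pilot status points towards estimation rather than towards significance tests.

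Four stronger readings are tempting, and the document does not support them.
- **That the laboratory values share the fault.** They are outside the ANOVA sentence, have one fixed two-point comparison, and carry a direction for anemia and vitamin D deficiency.
- **That multiplicity control is missing.** It may be in the unseen plan, so the 11-19% is context and not a finding in itself.
- **That the error rate should be counted over all pairwise visit comparisons.** That presumes pairwise tests are run, in which case the patterns would be separated. It cannot be combined with the complaint about an F test used alone.
- **That a significant result will choose the endpoint of the next trial.** The Discussion says the data will direct next steps, but states no such rule. Its remark about capturing benefits refers to the mixed methods together, not to a p-value.

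It is also fair that nothing in the article ranks the instruments or the visits for the surveys, so any particular choice of main contrast is a judgement for the sponsor.

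**Conclusion.** The point holds for the surveys only. Taken alone, the overall F test cannot answer whether scores improved or whether a gain lasted. At 130 participants it is significant in about 95% of trials under vanishing, lasting, delayed and adverse change alike, while the 3-month versus pretest contrast gives about 5% for a vanished gain and 92% for a lasting one. The percentages rest on an assumed 0.05 level, 0.3 SD shift, within-person correlation of 0.5 and no dropout. The equality across the four patterns needs only equal correlation and variance across visits. The 11-19% chance of at least one small p-value under no change is supporting context. Severity is low: the better method costs very little, and the study makes no confirmatory claim.

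**What to change.** Replace the ANOVA sentence with text along these lines:

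*For each survey instrument we will report the within-participant mean change from pretest to posttest and from pretest to 3-month follow-up, with 95% confidence intervals. The main preliminary outcome is the change in the UFS-QOL health-related quality-of-life score from pretest to 3 months. All other survey changes are exploratory; all will be shown, as estimates with confidence intervals and without claims of significance.*

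UFS-QOL at 3 months is an example. It fits the quality-of-life hypothesis in the Background and the timing of the laboratory comparison. The sponsor may name another score or contrast, provided that it is fixed before the outcome data are examined. The laboratory comparisons stay as written.

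The cost is a few sentences of text, with no new data and no extra participants. The downside is that an isolated significant result on another instrument or at another time point can no longer be presented as programme impact.

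### The ANOVA named for the survey scores does not account for repeated surveys of the same person or for delivery in 13 facilitated cohorts, and should be replaced by an analysis of within-person change that allows for cohort

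*Protocol article*

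**What the plan says.** All references are to the protocol article; no SAP is shown.

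- **Repeated measurement.** Quantitative methods: "participants will complete self-reported surveys during their participation in this study: pretest, posttest, and 3 month follow up".
- **Grouping.** Quantitative methods: "We anticipate 10-12 participants per cohort for a total of 13 cohorts, 7 at BMC and 6 at Emory/Grady". The Intervention section adds: "Each 1.5 h session will be facilitated by the study site principal investigator (PI), research staff trained in group facilitation". It also describes a model meant to work through relationships among group members.
- **Test.** Quantitative methods: "we will perform comparison of mean scores of the various validated survey instruments using analysis of variance (ANOVA) tests". No factor (time, site or cohort), participant term or cohort term is named, and one-way and repeated-measures forms are not distinguished.
- **Status.** Methods/design: "This pilot prospective cohort trial will utilize a concurrent mixed-methods design". On sample size, Quantitative methods says that "achieving a predetermined sample size for power was not necessary".

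The abstract differs on the number of groups: "planned recruitment of six cohorts of 10-12 participants at each institution", which makes 12 cohorts rather than 13. This needs reconciling, but does not affect the point below.

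**The concern.** The quantity of interest is change within a person. Two features of the design determine its standard error.

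1. **Person.** Three scores from one participant are positively correlated. An analysis that treats the visits as independent groups leaves stable differences between people in the error term. The standard error of change is then too large, and real change is easier to miss.
2. **Cohort.** People who share sessions and facilitators may change together. If so, an analysis that counts each person as an independent unit has too small a standard error and finds change too often. Only cohort variation in *change* matters here; a stable difference in level between cohorts cancels within persons.

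The two errors pull in opposite directions, so the reported p-values and intervals could be off either way, depending on which ANOVA is run. At stake is how far the pilot's estimates of survey change, and their precision, can be trusted when the next steps are decided.

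**Working it through.** **Plan's own figures.** 7 + 6 = 13 cohorts. With 10-12 people each, 13 × 10 = 130 to 13 × 12 = 156 participants; the midpoint is 13 × 11 = 143. (The abstract's 12 cohorts would give 120 to 144.) The document gives no SD, effect size, alpha, correlation or ICC, so there is no sample-size calculation to reproduce.

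**Assumptions.** Two-sided alpha 0.05; equal SD at each visit; within-person correlation r between visits; ICC of change as a range; an illustrative change of 0.25 SD.

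**Reading A: ordinary one-way ANOVA, no cohort effect on change**

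In SD units, the independent-groups standard error of a pre-post difference is √(2/N). The true one is √(2(1−r)/N). Reported/true = 1/√(1−r).

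| r | Reported SE / true SE |
|---|---|
| 0.5 | 1.41 |
| 0.6 | 1.58 |
| 0.7 | 1.83 |

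Power at N=143, r=0.6, change 0.25 SD:

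- Paired test: true SE = √(0.8/143) = 0.0748; 0.25/0.0748 = 3.34; power = Φ(3.34 − 1.96), about 0.91 to 0.92 (0.91 by simulation).
- Independent-groups comparison of two visits: SE = √(2/143) = 0.118; 0.25/0.118 = 2.11; power = Φ((2.11 − 1.96)/√0.4) = 0.60.
- One-way ANOVA across all three visits, simulated: 0.54 to 0.55. A rerun with the change reached by posttest and then held gave 0.55.

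Under this reading the simulated type I error of the three-visit test falls below 0.05: 0.015, 0.003 and below 0.001 for r of 0.3, 0.5 and 0.7.

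**Reading B: paired or repeated-measures analysis, cohort omitted**

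Design effect for mean change = 1 + (m − 1) × ICC. Actual two-sided type I error = 2 × (1 − Φ(1.96/√design effect)). With m = 11:

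| ICC of change | Design effect | Type I error, pre-post |
|---|---|---|
| 0.01 | 1.10 | 0.06 |
| 0.05 | 1.50 | 0.11 |
| 0.10 | 2.00 | 0.17 |

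For m from 10 to 12, type I error is 0.10-0.12 at ICC 0.05 and 0.16-0.18 at ICC 0.10. Repeated-measures ANOVA over all three visits, simulated with 13 cohorts of 11, gave 0.051-0.053 with no cohort effect, about 0.14 when cohort-by-visit variation is 5% of the within-person variance, and 0.22-0.23 when it is 10%.

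**Both features ignored.** One-way ANOVA with a cohort effect on change had simulated type I error from below 0.001 to 0.116, over r of 0.3-0.7 and a cohort share of 0-0.10. The direction is not determined.

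**What a valid analysis can deliver.** A t-test on 13 cohort mean changes (12 df; N=143, r=0.6, 0.25 SD; SE = 0.0748 × √design effect):

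| ICC of change | Effect / SE | Power |
|---|---|---|
| 0 | 3.34 | 0.87 |
| 0.05 | 2.73 | 0.71 |
| 0.10 | 2.36 | 0.58 |

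**The case against.** The strongest defence is that the text never says the observations will be treated as independent. ANOVA includes repeated-measures and nested forms, and with three surveys per person the repeated-measures reading is at least as natural. An article also commonly leaves error terms to the SAP. This stands to the extent that nobody can say the standard errors *are* wrong, only that they would be under a given form. It does not remove the point. The article does name a method, and neither usual form fits the design set out in the same section: one-way ANOVA mishandles the person, and repeated-measures ANOVA across visits still omits cohort.

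Further limits also stand:

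- Readings A and B exclude each other, so the power loss and the inflated type I error cannot be added together.
- No ICC is given. At 0.01 the inflation is trivial.
- The 0.91 power belongs to a test that ignores cohort. At an ICC of 0.10 the valid cohort-level test has power 0.58, close to the 0.55 of one-way ANOVA without a cohort effect. The case for changing is validity, not a guaranteed gain in power.

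A reader might infer three stronger points that the document does not support:

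- **Completers only.** Classical repeated-measures ANOVA drops people who miss a survey, but no such analysis is stated.
- **A Boston-Atlanta contrast of survey scores.** The Intervention section says that studying both hospitals "will help to detect any existing regional differences in implemention". That concerns implementation, which the article examines through interviews and process mapping. No ANOVA of scores by site is announced.
- **Corrupted inputs for the later trial.** The Discussion says the data will guide next steps, including a randomised trial. It does not say that ANOVA variances will size that trial, and variance components could still be estimated from the same data.

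**Conclusion.** The point holds in conditional form: the stated method does not, as worded, account for repeated surveys of the same person or for cohort delivery. Under one-way ANOVA without a cohort effect, the standard error of change is overstated by a factor of 1.41 to 1.83 (assumed r 0.5-0.7). Under a paired analysis without cohort, type I error for pre-post change is about 0.06 to 0.17 (assumed ICC of change 0.01-0.10), and there is no inflation if change does not vary by cohort. The correlation, ICC and effect size are assumptions; only the 13 cohorts, the 10-12 per cohort and the three surveys come from the document.

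Severity is moderate. This is a pilot seeking early signals, with no confirmatory test and no power claim, but a better-fitting method is available at little cost.

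**What to change.** In Quantitative methods, replace the ANOVA wording with an analysis of within-person change that accounts for cohort. One suitable form is a linear mixed model per instrument, with:

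- fixed effects for visit and site;
- random effects for participant and for cohort, including cohort-by-visit;
- a small-sample correction suited to 13 clusters;
- all available surveys included.

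A simpler valid alternative is to take each cohort's mean change and analyse the 13 values with a t-test.

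Either way, report change from pretest with a 95% confidence interval. From the mixed model, also report the participant and cohort variance components, with a note that 13 cohorts estimate the latter imprecisely.

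**Cost.** A few sentences and slightly more analysis work; no new data. If change varies by cohort, intervals will be wider than from a paired analysis that ignores cohort, and by more than a trivial amount: at ICC 0.10 the standard error rises by √2.0 = 1.41, and power for 0.25 SD is 0.58 against 0.87 at ICC 0. That is the precision the design actually provides.
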